### Discontinuation

Patients could withdraw or will be asked to withdraw from the study for the following reasons: (1) serious adverse events, (2) emergence of a new concurrent severe physical disease that is not well controlled, (3) exacerbation of any existing physical disease, (4) poor compliance, (5) any time when the patient asks to withdraw, and (6) certain situations in which the researchers consider it will be better for the patient to discontinue the treatment than to continue (e.g., increased suicide risk, participation in the study presents a significant burden to the patient, patient needs hospitalization). Patients will be clearly informed that they have the right to withdraw from the study at any time for any reason, during no matter screening or intervention period. The decision to withdraw a patient from the study will be made by the site principal investigator in consultation with the research team at the main research site.

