### Randomization and Blinding

In this study, a multi-center randomized controlled single-blind design has been adopted. Each site is being used as a stratified factor for stratified block randomization, and each site competes to enroll the subjects. We use the sealed envelope randomization method. Once a patient is deemed eligible to participate, researchers at the relevant site will open the particular numbered envelope to allocate the patient to his or her study condition, either medication plus AI-assisted psychotherapy group or medication alone group. As blinding to patients and researchers is not possible in psychotherapy trials, this trial will be single-blind. The researcher who does randomization is in charge of contacting participants and arranging independent rater to conduct certain assessment at each visit. The assessment time arranging and content in both groups are same. All the measurement will be assessed by independent raters who are unaware of the treatment allocation of patients.

Allocation of patients will be recorded in a separate assessment log which cannot be accessed by raters. In order to ascertain the blinding, patients will be informed not to reveal their treatment during the blinding assessments, and the raters will be asked to document whether patients told them the allocation. The statisticians will also be blind to group allocation.

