#### AI-Assisted Psychotherapy

##### Technical Overview and Customization

Patients assigned to the medication plus AI-assisted psychotherapy group will receive 12 weekly sessions of AI-assisted psychotherapy. The therapist is XIAO AN. XIAO AN is the name of the virtual psychotherapist designed by Shanghai Mental Health Center (SMHC). The Chinese character for “AN” means quiet, peaceful and safe, which symbolizes a state of mind free from anxiety.

XIAO AN is an AI-based psychological chatbot app which is designed to address the current situation of lack of psychotherapy resources, but not to replace the role of therapists. The knowledge structure and content of XIAO AN were selected, discussed and developed by psychiatric and psychological professionals at SMHC. User experience testing was conducted among a group of medical students and hospital staff, including medical-related staff and non-medical-related staff. We have been continually optimizing the structure and content of XIAO AN over the last year.

The app is installed on an Android tablet. Patients are treated by XIAO AN in a particular consulting room for this study in the relevant hospital. The researchers monitor the patients' treatment via video, and as XIAO AN does not have the crisis management function, if there is a risk of self-injury or suicide, the researchers will recommend patients to pause the process and refer the patient to emergency medical treatment.

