## Statistical Analysis

The aim of this trial is the explore whether medication plus AI-assisted psychotherapy has greater efficacy than medication alone in the treatment of anxiety disorders. The principal analyses will be conducted using the intention-to-treat sample. One-sided 5% significance level will be adopted, and corresponding 95% CIs will be calculated whenever possible. Continuous outcomes, the HAMA score reduction from baseline to week 2 and week 12, will be analyzed using analysis of variance and general linear mixed models. Treatment allocation, time, and interaction between treatment allocation and time will be the main predictors. Gender, age, education level, and baseline scores will be the covariates and treatment site will be a random effect in the model. The mixed models will be estimated using restricted maximum likelihood. The least square mean difference between the groups at 12 weeks will be tested as the main analysis. Other analyses will include comparisons at weeks 2, 4, 8, and 12, with adjustment for multiple testing. Multiple comparison issues of *post-hoc* analysis will be handled using Bonferroni adjustment. Dichotomous variables will be compared between groups using the chi-square test, Fisher's exact test, or generalized estimating equation. The above analyses will also be conducted with the follow-up data.

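### The discontinuation rule merges stopping treatment with leaving the study, so poor compliance or a serious adverse event can end the HAMA assessments that the intention-to-treat comparison at week 12 needs

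*Protocol article*

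**What the plan says.** The Discontinuation section opens with "Patients could withdraw or will be asked to withdraw from the study for the following reasons". Six reasons follow. They include serious adverse events, new or worsening physical disease, "4) poor compliance" (with no definition or threshold), the patient's own request, and "certain situations in which the researchers consider it will be better for the patient to discontinue the treatment than to continue". The examples for the last reason include increased suicide risk and need for hospitalisation. On who decides, the section says "The decision to withdraw a patient from the study will be made by the site principal investigator". The main centre's team is to be consulted. Randomization and Blinding states "As blinding to patients and researchers is not possible in psychotherapy trials, this trial will be single-blind"; raters and statisticians are the blinded parties.

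Statistical Analysis says "The principal analyses will be conducted using the intention-to-treat sample". Its main test is the least-squares mean difference at week 12, with mixed models estimated by restricted maximum likelihood. Participant Timeline has every participant assessed at baseline, at weeks 2, 4, 8 and 12, and 3 and 6 months after treatment. The Medication section asks for non-adherence to be recorded.

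**The concern.** Stopping treatment and leaving the study are different events. An intention-to-treat comparison at week 12 needs the week-12 HAMA from every randomised patient who still consents to be assessed, including those who stopped treatment or did not comply. The Discontinuation section treats the two events as one. Its last reason is worded as discontinuing treatment, yet it stands in a list of reasons for leaving the study. Nothing there provides for assessment afterwards.

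The patients affected are unlikely to resemble those who remain, because removal follows non-compliance, a serious adverse event or raised risk. Those involved in the decision are not described as blinded. The arms also differ in what there is to comply with: "Patients assigned to the medication plus AI-assisted psychotherapy group will receive 12 weekly sessions of AI-assisted psychotherapy", whereas controls have medication and the scheduled visits only. At stake are primary-endpoint data that no later analysis can recover once the visits have not taken place.

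**Working it through.** **Passages side by side**

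- *Discontinuation and Statistical Analysis.* The first can end a patient's participation for poor compliance. The second compares the arms as randomised at week 12, whatever the compliance.
- *Discontinuation and Participant Timeline.* The timeline has each participant assessed through week 12 and follow-up. A patient withdrawn from the study cannot be.
- *Discontinuation and Medication.* One makes poor compliance a reason to leave; the other asks for non-adherence to be recorded, which presupposes that the patient is still observed.

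**What the mixed model recovers.** It uses each patient's HAMA values up to withdrawal and is valid if, given those values and the covariates, withdrawal does not depend on the unseen later scores. A serious adverse event or raised suicide risk arising between visits need not show in the last recorded HAMA, and the gap from week 8 to week 12 is four weeks. The section also names analysis of variance and, for dichotomous outcomes, chi-square and Fisher tests. Applied to observed data, these make no use of earlier visits.

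**The plan's own figures.** Sample Size gives 354 per arm, 708 in total, with 20% drop-out. The 354 is nearly reproduced by 60% vs 70% response, one-sided 5%, 80% power: 281 per arm, and 281/0.8 = 352. The 60% control rate is inferred, not stated. The present point does not depend on it. Planned loss is 0.20 × 708 = 141.6, about 142 patients, leaving 354 × 0.8 = 283 per arm. The document does not say how much of this would come from the withdrawal rule.

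**Illustration on HAMA.** Assume no true difference and the same full-arm mean m in both arms. Let p be the share removed and d the amount by which removed patients score worse than retained ones. The retained mean is m − p·d, so the observed-case bias in favour of the AI arm is (p_AI − p_control) × d. Both inputs are assumptions.

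- Equal loss of similar patients, 20% and 20%: 0 × d = 0.
- 25% vs 15%, which keeps 20% overall, d = 3: 0.10 × 3 = 0.3 points.
- The same loss, d = 5: 0.10 × 5 = 0.5 points.
- With the arms reversed, the sign reverses.

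**Illustration on response.** Assume 50% true response in both arms, 15% removed from control and 25% from the AI arm, and 30% response among the removed.

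- Control, observed: (0.50 − 0.15 × 0.30)/0.85 = 0.535.
- AI arm, observed: (0.50 − 0.25 × 0.30)/0.75 = 0.567.
- Spurious difference: 3.1 percentage points. The nominal 5% one-sided error becomes about 19%.
- With 40% or 20% response among the removed, the difference is 1.6 or 4.7 points and the error about 10% or 30%. With 50% it is 0 and 5%.

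Both illustrations are for observed cases. The mixed model would remove the part of the HAMA bias that earlier visits and covariates explain; how much cannot be computed from the document.

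**The case against.** The strongest reply is that this is a condensed article. Procedures after discontinuation may stand in the full protocol, nothing says that data before withdrawal are discarded, and the mixed model retains them. The last two points stand, and they limit the claim. The first does not answer it: the rule on leaving the study is stated here, and an analysis plan cannot supply scores that were never collected.

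A reader might go further and infer that the rule will remove more patients from the AI arm and so favour it. The document does not support that as a fact. It gives no withdrawal rate by arm. The 12-week prescription requirement applies to both arms, and the section does not say whether compliance means medication, visits or sessions. The article does say "The researchers monitor the patients' treatment via video", but the stated response to risk seen there is to recommend a pause and refer the patient, not to withdraw the patient. Controls, who know their allocation, could leave more often. Unequal loss is plausible because only one arm has weekly hospital sessions, but its direction is open.

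A reader might also say that the rule defeats intention to treat. That is too strong. Randomised patients stay in the analysis set with the visits they have. Nor does the text say that such patients must be removed: they may choose to withdraw or be asked to, and the patient's own request is a right that no amendment should touch.

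**Conclusion.** The point holds in this form: the Discontinuation section, as written, allows non-compliance and on-treatment events to end HAMA assessment, and this undermines the intention-to-treat comparison at week 12. The result then leans on a missing-at-random assumption that is doubtful for these reasons of removal. This rests on reading withdrawal from the study as the end of assessment, which is its plain meaning here.

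The size is not known. The range runs from zero, with equal loss of similar patients, to 0.3 to 0.5 HAMA points for observed cases under the assumed 10-point gap and 3 to 5 point deficit, in either direction and smaller under the mixed model. The document gives no standard deviation for HAMA, so these figures cannot be expressed as a share of the difference the trial can detect. The case for change rests on the loss being irrecoverable and cheap to avoid, not on a demonstrated bias.

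**What to change.** Split the section in two.

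1. *Discontinuation of study treatment.* Leave the clinical reasons, and the investigators' judgement on them, as they stand.
2. *Withdrawal from the study.* State that a randomised patient who stops treatment or does not comply remains in the study and is assessed by the blind rater at every remaining scheduled visit to week 12 and at 3 and 6 months, unless consent to follow-up is withdrawn. Remove poor compliance as a reason to end study assessments.

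In Statistical Analysis, state that HAMA data collected after treatment discontinuation enter the primary intention-to-treat analysis.

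The cost is a protocol amendment and staff time for visits already in the schedule, now also held for patients who have stopped treatment. Trial Status reports that recruitment is under way, so the change should be made promptly; each week-12 score missed in the meantime is lost.

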## Measurements

Our primary efficacy measurement is the Hamilton Anxiety Scale (HAMA). Response is defined by a 50% reduction at least in total HAMA score. Secondary efficacy measurement is improvement in treatment at an early stage (score reduction in HAMA ≥25% at week 2 of treatment). Incidence of adverse events will be also recorded.

Other measurements include the Hamilton Depression Scale (HAMD-17), Clinical Global Impression (CGI), Treatment Emergent Symptom Scale (TESS), Social Disability Screening Schedule (SDSS), World Health Organization Quality of Life Brief Form (WHO-QOL-Brief), Generalized Anxiety Disorder-7 (GAD-7), Patient Health Questionnaire-9 (PHQ-9), Insomnia Severity Index (ISI), the Self-Assessment Scale of the Overall Efficacy and Satisfaction of Patients (SASE), Toronto Alexithymia Scale (TAS-20), Cognitive Emotion Regulation Questionnaire (CERQ), Liebowitz social anxiety scale (LSAS), Panic Disorder Severity Scale (PDSS). The HAMD-17, CGI, TESS, SDSS, PDSS will be administered by independent blind raters. Other scales will be self-assessed. Paradigm of negative pictures stimulation, facial expression emotion analysis, phonetic and semantic analysis are also included.

## Statistical Analysis

The aim of this trial is the explore whether medication plus AI-assisted psychotherapy has greater efficacy than medication alone in the treatment of anxiety disorders. The principal analyses will be conducted using the intention-to-treat sample. One-sided 5% significance level will be adopted, and corresponding 95% CIs will be calculated whenever possible. Continuous outcomes, the HAMA score reduction from baseline to week 2 and week 12, will be analyzed using analysis of variance and general linear mixed models. Treatment allocation, time, and interaction between treatment allocation and time will be the main predictors. Gender, age, education level, and baseline scores will be the covariates and treatment site will be a random effect in the model. The mixed models will be estimated using restricted maximum likelihood. The least square mean difference between the groups at 12 weeks will be tested as the main analysis. Other analyses will include comparisons at weeks 2, 4, 8, and 12, with adjustment for multiple testing. Multiple comparison issues of *post-hoc* analysis will be handled using Bonferroni adjustment. Dichotomous variables will be compared between groups using the chi-square test, Fisher's exact test, or generalized estimating equation. The above analyses will also be conducted with the follow-up data.

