**Methods:**

We will recruit patients in eight hospitals in China. Seven hundred and eight patients with anxiety disorders will be randomly allocated on a 1:1 basis to either medication plus AI-assisted psychotherapy group, or medication alone group. We have built an AI psychotherapy robot named XIAO AN. In this study we will deliver psychotherapy to patients in the medication plus AI-assisted psychotherapy group. Patients will be assessed at baseline and at the end of week 2, 4, 8, and 12. Follow-up assessments will be conducted at 3 and 6 months posttreatment. The primary outcome is change of Hamilton Anxiety Rating Scale (HAMA) score from baseline the end of 12-week treatment. A secondary efficacy outcome will be improvement in treatment at an early stage (score reduction in HAMA ≥25% after 2 weeks of treatment). Other measurements include Hamilton Depression Scale, Clinical Global Impression, Treatment Emergent Symptom Scale, Social Disability Screening Schedule, Insomnia Severity Index and so on. Scales will be assessed by independent raters who are blind to treatment allocation and analyses will be conducted by a statistician who is also blind to treatment allocation.

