### Participants and Eligibility

Patients who are eligible need to (a) be between the ages of 18–60 years, (b) meet DSM-5 criteria for an anxiety disorder, including generalized anxiety disorder, panic disorder, agoraphobia, social anxiety disorder, and specific phobia, (c) score>14 on the Hamilton Anxiety Rating Scale (HAMA), (d) be psychotropic medication naïve or have discontinued medication for at least 8 weeks prior to the screening visit, (e) be able to use a computer and smart phone skillfully, and (f) provide written informed consent.

Candidates will be excluded if they: (a) have a severe concurrent medical condition, (b) are at high self-injury or suicide risk, (c) are suffering from a serious physical disease, neurological disease, or substance abuse, (d) have a lifetime history of other DSM-5 mental disorders, (e) are experiencing major life changes, (f) have received systematic drug therapy, psychological therapy or modified electric convulsive therapy (MECT) treatment within 3 months before enrollment, (g) are pregnant or in the lactation period.

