### Participant Timeline

Each participant will complete the psychological assessment including symptom measurement at baseline and at the end of weeks 2, 4, 8, and 12. Follow-up assessments will be conducted at 3 and 6 months after the 12-week treatment (Table 1).

**Table 1 T1:** Study assessment tools and assessment time schedule.

**Timepoint**	**Enrollment**	**Randomization**	**Postrandomization**					
	**–t1**	**t0**	**t1**	**t2**	**t3**	**t4**	**t5**	**t6**
		**0 weeks**	**2 weeks**	**4 weeks**	**8 weeks**	**12 weeks**	**3 months**	**6 months**
MINI6.0.0	■							
Demographic information	■							
HAMA	■	■	■	■	■	■	■	■
HAMD-17	■	■	■	■	■	■	■	■
GAD-7		■	■	■	■	■	■	■
PHQ-9		■	■	■	■	■	■	■
ISI		■				■	■	■
CGI			■	■	■	■	■	■
TESS			■	■	■	■	■	■
SASE						■	■	■
SDSS		■	■	■	■	■	■	■
WHO-QOL-Brief		■	■	■	■	■	■	■
TAS-20		■				■	■	■
CERQ		■				■	■	■
LSAS		■	■	■	■	■	■	■
PDSS		■	■	■	■	■	■	■

*MINI6.0.0, Mini International Neuro-psychiatry Interview (Version 6.0.0); HAMA, Hamilton Anxiety Rating Scale; HAMD-17, the 17-item Hamilton Depression Scale; GAD-7, Generalized Anxiety Disorder-7; PHQ-9, Patient Health Questionnaire-9; ISI, Insomnia Severity Index; CGI, Clinical Global Impression*.

*TESS, Treatment Emergent Symptom Scale; SASE, Self-Assessment Scale of the Overall Efficacy and Satisfaction of Patients; SDSS, Social Disability Screening Schedule; WHO-QOL-Brief, World Health Organization Quality of Life Brief Form; TAS-20, Toronto Alexithymia Scale; CERQ, Cognitive Emotion Regulation Questionnaire; LSAS, Liebowitz social anxiety scale; PDSS, Panic Disorder Severity Scale*.

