### Sample Size

We calculated the sample size based a significance level of 0.05 and with power of 0.8. Previous literature showed that the effective rate of single-drug combination psychotherapy (the reduction rate of HAMA after treatment is greater than or equal to 50% as effective treatment) was 70%, and the effective rate of single-drug therapy was 50%. We assumed that the medication plus AI-assisted psychotherapy group had a 10% higher response rate than the medication alone group. Assuming 20% as drop-out rate, the target enrollment is 354 patients in each group, and 708 in total (17).

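### HAMA is rated twice before treatment; adding the screening rating as a second covariate would give the primary model a free but small gain in precision

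*Protocol article*

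**What the plan says.** Table 1 of the protocol article ("Study assessment tools and assessment time schedule") marks HAMA in all eight columns. Two of these come before treatment: -t1, labelled enrollment, and t0, labelled randomization and week 0. The screening rating is needed because entry requires a HAMA score above 14 (Participants and Eligibility).

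The abstract defines the endpoint: "The primary outcome is change of Hamilton Anxiety Rating Scale (HAMA) score from baseline the end of 12-week treatment". The Statistical Analysis section names the main test: "The least square mean difference between the groups at 12 weeks will be tested as the main analysis". It specifies the adjustment as follows: "Gender, age, education level, and baseline scores will be the covariates", with site entered as a random effect. It does not say whether the baseline HAMA is the screening rating, the t0 rating or both. The Participant Timeline text describes one baseline occasion: "symptom measurement at baseline and at the end of weeks 2, 4, 8, and 12". The interval between -t1 and t0 is not given, nor is any standard deviation or correlation for HAMA.

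**The concern.** A single HAMA rating measures a patient's severity with error. Two ratings taken before treatment usually predict the week-12 score better than one, and better prediction lowers the residual variance of the adjusted treatment difference. The second rating is already scheduled. It should be complete for everyone randomized, because eligibility depends on it. If the primary model uses only t0, some precision on the main contrast may be given up for nothing. At stake is a little power and a slightly narrower confidence interval. The validity of the test is not in question.

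**Working it through.** **Number analysed.** Sample Size gives "a significance level of 0.05 and with power of 0.8", a 10-point difference in response, 20% dropout and 354 per group. With 70% against 60%, a one-sided 5% test and pooled variance:

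n = [1.645·√(2·0.65·0.35) + 0.842·√(0.70·0.30 + 0.60·0.40)]² / 0.10² = 281 per arm, and 281/0.8 = 352.

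This is close to 354. The 60% control rate is inferred from the fit and is not stated. The figure serves here only to fix the evaluable number: 354 × 0.8 = 283 per arm, 566 in total.

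**Formulas.** Once t0 HAMA is a covariate, analysing the change from t0 or the week-12 score gives the same treatment contrast. Let r₁ be the correlation of t0 with week 12, r₂ that of screening with week 12, and ρ that between the two ratings. As a simplification, take complete data at week 12 and ignore the other covariates.

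- t0 only: residual variance = 1 − r₁²
- both ratings: residual variance = 1 − r₁² − (r₂ − ρr₁)²/(1 − ρ²)
- if r₁ = r₂ = r, the second line becomes 1 − 2r²/(1 + ρ)

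**Equal correlations (assumed).** Power is one-sided at 5% with 283 per arm, for an effect that has 80% power with t0 alone.

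| r | ρ | Residual variance, t0 only | Both | Fall | Power |
|---|---|---|---|---|---|
| 0.3 | 0.8 | 0.910 | 0.900 | 1.1% | 80.4% |
| 0.3 | 0.9 | 0.910 | 0.905 | 0.5% | 80.2% |
| 0.4 | 0.7 | 0.840 | 0.812 | 3.4% | 81.2% |
| 0.5 | 0.9 | 0.750 | 0.737 | 1.8% | 80.6% |
| 0.5 | 0.7 | 0.750 | 0.706 | 5.9% | 82.1% |
| 0.5 | 0.6 | 0.750 | 0.688 | 8.3% | 83.0% |

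The middle case (0.4, 0.7) lowers the standard error by 1.7%. In patients that is 283 × 0.0336 ≈ 10 per arm. The most favourable row is worth 283 × 0.0833 ≈ 24 per arm. A corner such as r = 0.6, ρ = 0.6 would give 14%. It requires the two pre-treatment ratings to agree with each other no better than either agrees with a score after 12 weeks of treatment, so I leave it out of the range.

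**Unequal correlations (assumed).** The screening rating is earlier and truncated, so it may predict less well than t0.

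- r₁ = 0.4, r₂ = 0.3, ρ = 0.7: added R² = (0.30 − 0.28)²/0.51 = 0.0008. Residual variance goes from 0.8400 to 0.8392, a fall of 0.1%.
- r₁ = 0.5, r₂ = 0.4, ρ = 0.7: added R² = (0.40 − 0.35)²/0.51 = 0.0049. Residual variance goes from 0.7500 to 0.7451, a fall of 0.7%.
- r₂ = ρr₁ (for example 0.28 = 0.7 × 0.4): no gain.

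**Truncation at entry.** A simulation kept only screening scores above 14, with an assumed untruncated mean of 18 or 22 and SD of 6. At r = 0.5 and ρ = 0.7 the fall was 4.1% and 5.0% respectively, against 5.9% without truncation. Power was 81.4% and 81.7%, against 82.1%.

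**Cost.** One more covariate uses one degree of freedom, roughly 1/566 = 0.2% in variance. In the 0.1% case this cancels the gain.

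**The case against.** The strongest reply is that nothing in the document is wrong. Adjusting for one baseline score is standard and valid. The article never says that the screening HAMA is excluded, and a condensed article may leave the definition of baseline to the full protocol or the analysis plan. This stands: that the screening value goes unused is an inference from the natural reading. The reply adds that the gain depends on correlations the documents do not report, and that it shrinks when the two visits are close together, when screening predicts less well than t0, or when truncation is allowed for. That also stands, and it is why the range starts at about zero.

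A reader might go further and infer that the baseline is ambiguous, so that response and early-improvement rates could be counted from the truncated screening score and inflated by regression to the mean. The documents do not support this. The timeline sequence of a baseline followed by weeks 2, 4, 8 and 12 matches t0 to t4 in Table 1, and no section uses the screening score as the reference. Any such inflation would also arise in both arms, so it would affect the reported rates more than the randomized contrast.

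A reader might also want the extra covariate in adjusted analyses of the binary HAMA outcomes. The Statistical Analysis section names no covariates for those, so the point is confined to the primary mixed model.

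**Conclusion.** The point holds as an optional improvement. Two pre-treatment HAMA ratings are scheduled, the model most naturally uses one, and adding the other is unbiased and nearly free. Under the assumed correlations (0.3 to 0.5 with week 12 when the two ratings predict equally, 0.6 to 0.9 between them, with the screening correlation also allowed to be lower), residual variance at week 12 falls by about 0% to 8%, with about 3% in the middle case. In power that is at most about 3 points from a starting value of 80%, and about 1 point in the middle case. The gain is negligible if the two ratings nearly coincide or if screening carries no information beyond t0. The planned sample size does not change.

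**What to change.** In the analysis plan, before unblinding, add the screening (-t1) HAMA as a second covariate beside the t0 HAMA in the primary mixed model for the week-12 difference. Keep t0 as the reference for the change score and for the 25% and 50% reductions, and say so in one sentence, so that the new term alters no endpoint. If the t0 rating turns out to be the screening rating carried forward, leave the extra term out, because it would add nothing. The cost is one degree of freedom, one more model term and a line of wording. No visit or data item is added.

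### Holm's step-down could replace Bonferroni, the only multiplicity method named: same family-wise error control, never less power (an optional gain for supportive comparisons)

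*Protocol article*

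**What the plan says.** All the relevant text is in the Statistical Analysis section of the protocol article.

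- **Main test.** It is a single comparison: "The least square mean difference between the groups at 12 weeks will be tested as the main analysis".
- **Visit-wise comparisons.** These come after it as supportive work: "Other analyses will include comparisons at weeks 2, 4, 8, and 12, with adjustment for multiple testing". The sentence does not say which adjustment.
- **Named method.** The next sentence is about post-hoc work, and says that multiple comparisons in such "analysis will be handled using Bonferroni adjustment". No other multiplicity method appears in the article.
- **Level and intervals.** "One-sided 5% significance level will be adopted, and corresponding 95% CIs will be calculated whenever possible". The intervals are not described as simultaneous or multiplicity-adjusted.

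The Sample Size section rests on response rates and claims no power for the comparisons by visit.

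**The concern.** With four comparisons and a one-sided 5% family level, Bonferroni tests each visit at 0.05/4 = 0.0125, whatever the other visits show. Holm starts at the same threshold but relaxes it after each rejection, with the same guarantee on the family-wise error. If the treatment works at several visits, which is plausible for a 12-week course, plain Bonferroni can leave a visit non-significant that Holm would declare significant from the same data at the same error level.

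At stake is how clearly the trial can describe when a benefit appears. Early improvement interests the investigators: the article lists HAMA reduction from baseline to week 2 among its continuous outcomes, and a 25% reduction at week 2 as a secondary efficacy measure. That responder measure is dichotomous and lies outside this family of tests, so the link to it is indirect.

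**Working it through.** **No planned figure to reproduce.** The article states no power or threshold for the visit-wise comparisons. Its target of 354 per group enters only through the number evaluable.

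**Inputs from the article.** One-sided level 0.05; four visits; 354 per group; 20% drop-out. Evaluable per arm: 354 × 0.8 = 283.2, taken as 283.

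**Inputs assumed, not in the article.** Standardised differences d at each visit, and correlations between the visit statistics.

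**Thresholds for four tests.** Bonferroni uses 0.0125 for every test. Holm compares the ordered p-values, smallest first, with 0.05/4 = 0.0125, 0.05/3 = 0.0167, 0.05/2 = 0.025 and 0.05/1 = 0.05, stopping at the first failure. Each Holm threshold is at least 0.0125, so a Bonferroni rejection is always a Holm rejection.

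**Bonferroni power by formula.** Power = Φ(d·√(n/2) − z), with z = 2.241 for a one-sided 0.0125. For d = 0.10: 0.10 × √(283/2) = 1.190, and Φ(1.190 − 2.241) = 14.6%. For d = 0.20: Φ(2.379 − 2.241) = 55.5%. The simulation agrees with both.

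**Simulation.** 400,000 draws of correlated one-sided z-statistics with means d·√(283/2). In the first four rows the correlation is 0.75 between adjacent visits and decays with distance.

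| Assumed d, weeks 2/4/8/12 | Bonferroni power, % | Holm power, % | Gain, points |
|---|---|---|---|
| 0.10/0.15/0.20/0.25 | 15/32/55/77 | 27/42/61/79 | 12.5/9.7/5.4/1.7 |
| 0.08/0.14/0.19/0.21 | 10/28/51/60 | 20/36/55/63 | 10.0/8.2/4.2/3.2 |
| 0/0/0/0.21 | week 12: 60.2 | week 12: 60.2 | 0.0 |
| 0.10/0.15/0.20 (week 12 left out of the family) | 17/37/60 | 28/43/62 | 10.3/6.2/2.0 |
| 0.10/0.15/0.20/0.21, adjacent correlation 0.5 | 15/32/55/60 | 24/41/61/65 | 9.4/8.4/5.2/5.2 |

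An equal correlation of 0.6 between all visits gives gains within about 1 point of the first two rows.

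**Error control.** With no effect at any visit, the chance of at least one false rejection is the same for both methods: 0.036 at adjacent correlation 0.75 and 0.043 at 0.5. No draw had a Bonferroni rejection that Holm missed. When only week 12 has an effect, each null visit is rejected in about 2.0% of draws under Holm against 1.2% under Bonferroni, still within the 5% family limit.

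**What Holm does not change.** The chance of at least one rejection is identical (0.81 for both in the first row). The gain lies in how many visits are declared, not in whether any is.

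**The case against.** The strongest reply is that this is a preference and not an error. Bonferroni is valid under any dependence, is prespecified and errs on the safe side; no bias or excess false-positive risk follows from it. That stands, and it limits the point to an optional improvement.

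A reader might infer that the article assigns Bonferroni to the weekly comparisons. It does not: the sentence on those weeks names no method, and Bonferroni is tied to post-hoc analysis. Reading the two adjacent sentences together is natural, because contrasts taken after a treatment-by-time model are often called post-hoc, but it remains an inference.

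A reader might also infer that power is lost for no return, or that the trial's main answer is at risk. Neither is supported. Bonferroni offers simple simultaneous intervals that match its tests, and Holm does not. The main analysis is one separate test at week 12, and the visit-wise results are supportive. The interval argument has limited force here, because the article asks only for 95% intervals and does not call them simultaneous.

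The size of the gain is also fairly challenged. It rests on assumed effects and correlations and applies the full 20% drop-out already at week 2. The largest figure counts week 12, tested alone as the main analysis, as a strong fourth member of the family. Even with Holm, week-2 power in the first two rows is only 20% to 27%, so the early comparison stays weak.

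**Conclusion.** The point holds as an optional, inexpensive improvement. It is not a defect in the plan. Bonferroni is the only method named, for post-hoc analysis and apparently for the four visits as well, and Holm gives the same family-wise error control while never rejecting less. That much is mathematical and needs no assumption about the data.

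The size does need assumptions. With 283 per arm, a one-sided 5% family level and effects at several visits, the gain is roughly 2 to 13 points per visit, largest where the effect is small and later visits are strong. It is essentially zero if only one visit has an effect. The week-12 main analysis, the sample size and the trial's principal conclusion do not change.

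**What to change.** In the Statistical Analysis section, name Holm's step-down adjustment in place of Bonferroni and state which comparisons it covers. For example:

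> Multiplicity will be handled by Holm's step-down procedure, applied separately to the between-group comparisons by visit and to the post-hoc analyses. Holm-adjusted p-values will be reported beside 95% confidence intervals, labelled as unadjusted for multiplicity.

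This also removes the doubt about which method the weekly comparisons use. The cost is one or two sentences and a software option, with no extra patients or data. The downside is that an unadjusted interval may exclude zero while its adjusted p-value is not significant. If the investigators prefer intervals that match the tests, keeping Bonferroni is defensible; the text should then say that it covers the visit-wise comparisons and that the intervals are simultaneous.
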